### The RISK^INDEX^

The RISK^INDEX^ was developed using ML technology at the MUMC + and aims to predict all-cause 31-day mortality for adults ED patients [16]. The score is calibrated ranging from 0 to 100, where a high RISK^INDEX^ indicates a high risk of mortality, and a low RISK^INDEX^ indicates a low risk of mortality.

The RISK^INDEX^ is based on age, sex and the results of at least four routine laboratory tests in the ED performed within the first two hours of the ED visit. All laboratory values are used to calculate the RISK^INDEX^ with the exception of tests that are prevalent less than 0.01%. The most commonly ordered laboratory values are creatinine, complete blood count (CBC), sodium, potassium, C-reactive protein (CRP), blood urea nitrogen (BUN), glucose, alanine transaminase (ALAT), aspartate aminotransferase (ASAT), creatine kinase (CK), and platelets. A detailed prescription regarding the RISK^INDEX^ is shown in Supplemental data.

### Allocation and blinding

Patients will randomly be allocated in a 1:1 ratio to the intervention group or the control group (Supplemental Fig. 1). This randomization is automatically performed by a computer system using block randomization of 100 patients. Electronic randomization is performed automatically using an online program. The allocation is presented within 2 h after presentation of the patient to the ED. The study is an open-label study that is not blinded for physicians.

### Follow-up

After the patients’ visit to the ED, the follow-up regarding 31-day mortality and other endpoints will be checked by reviewing the medical records. In the Netherlands, all deaths are registered by the municipal administration office, and these data are linked to the medical records.

### Drop-out/withdrawal

Patients can leave the study at any time for any reason without any consequences if they wish to do so. The investigator can decide to withdraw a patient from the study for urgent medical reasons. If a patients withdraws from the study, the data up until that moment will be used in study analysis. Data of patients who are unwilling to participate in the study after a deferred consent procedure took place will be deleted and will not be used in the study analysis. The patient will not be replaced, as the study design takes less than 10% drop-out into account. Considering the short duration of the study follow-up, the expected drop-out rate is low.

### Adverse event monitoring

The presentation of the RISK^INDEX^ to the ED physician and the possibly resulting change in the medical treatment plan is considered to have a low risk of undesirable outcomes. The 31-day mortality is expected to remain around the usual average, which is approximately 10%. Possible complications will be closely monitored by the researchers and will be followed until they have abated, or until a stable situation has been reached.

### Data collection methods

The researcher will collect the results of laboratory tests, which are already routinely measured in the ED for internal medicine patients. The laboratory data, sex and age are used to determine the RISK^INDEX^. In addition, the physician will provide answers on the questions regarding their clinical intuition.

Patient characteristics will be retrieved from medical records and include: demographics (age, sex), comorbidities, mode of transportation to the ED (ambulance or own transport), reason for ED visit (according to the international classification of diseases (ICD-) 10 system) [23], date and time of the ED visit, and triage category. The following vital signs will be retrieved: heart rate (HR), blood pressure (BP), respiratory rate (RR), oxygen saturation, temperature, and Glasgow coma scale (GCS). Furthermore, we will collect data on hospital admission, admission to intensive care unit (ICU), treatment restrictions and all-cause mortality within 31 days after the ED visit. The data regarding patient characteristics, vital signs and outcomes will be retrieved manually. To ensure the quality of these data (i.e. to check whether the data are correct and complete), we will perform a double-check by another member of the research team and/or the study monitor. The retrieval of data regarding the results of laboratory tests and the results of the RISK^INDEX^ will be automated.

Data will be stored anonymously in an online electronic case record form in CASTOR, which is available for researchers in all participating study centers. Personal data will be handled in compliance with the EU General Data Protection Regulation and the Dutch Act on Implementation of the General Data Protection Regulation, as well as the “Algemene Verordening Gegevensbescherming)” (law on the protection of general data) [24, 25].

The patient identification code list will be stored digitally and encrypted with a strong password. The patient data and documents will be stored for 15 years. Data may be used for other studies which are in line with the current study, as approved by the METC. Data monitoring will be performed by the Clinical Trial Center Maastricht (CTCM).

### Sample size

This pilot trial has an explorative aim, providing future trials with estimates of effect sizes and potential clinical impact of the RISK^INDEX^. This study aims to provide robust estimates for the likely recruitment and retention rates and give an indication of the potential variability in the proposed outcome measures, which will in turn be used to inform the power calculation for a future definitive randomized controlled trial (RCT). We calculated a required sample size of 784 patients to detect a 2% difference in the number of changes in medical treatment after presentation of the RISK^INDEX^ between the control group and the intervention group with a power of 0.8.

Yearly, approximately 5,500 patients are treated by an internal medicine specialist at the ED of MUMC+. Considering fluctuations in the number of patients presenting to the ED and moments of crowding, there may be moments where there will not be enough time to include patients and/or to complete the questionnaires. Therefore, we expect a total sample size of 1300 patients during the inclusion period.

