## Methods

### Study objectives and endpoints

The primary objective of this study is to assess the prognostic accuracy and the clinical impact of the RISK^INDEX^ prediction model. Secondary objectives of this study are to assess: (1) the number and type of changes in medical treatment after presentation of the RISK^INDEX^ to the ED physician; and (2) the prognostic accuracy of the RISK^INDEX^ as compared to that of the physician’s clinical intuition and that of other clinical prediction models (e.g. MEWS, SOFA, RISE UP score).

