### Trial design and setting

The MARS-ED study is designed as an investigator-initiated, open-label, randomized, non-inferiority, pilot clinical trial. Adult patients presenting to the ED who are primarily assessed and treated by an internal medicine specialist will be randomized in a 1:1 ratio to the control group or the intervention group. This study is not blinded, since the physician needs to be informed of the RISK^INDEX^ in order to assess the size of the clinical impact of the RISK^INDEX^.

The study will be conducted in the ED of the MUMC+, which is a secondary/tertiary care medical center in the Netherlands, with 5,500 patients visiting the ED for assessment by an internal medicine specialist each year. In contrast to many other countries where patients can visit the ED without referral by a health care professional (open access ED), nearly all ED patients in the Netherlands after referred after an initial triage process by a general practitioner, a medical specialist or ambulance.

This study protocol is designed in accordance with the Standard Protocol Items: Recommendations for Interventional Trials - Artificial Intelligence (SPIRIT-AI) and the Consorted Standards of Reporting Trials (CONSORT) guidelines (Supplementary Table 1) [17, 18]. This study has been approved by the medical ethical committee (METC) of the MUMC + on June 21st 2022 (METC 21–068) and is registered at clinicaltrials.gov (NCT05497830). The study will be conducted according to the principles of the Declaration of Helsinki (version 2013, July 9th 2018) and in accordance with the standards of Good Clinical Practice. The study is expected to last from September 2022 to September 2024.

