**Questionnaire regarding medical treatment changes (intervention group only)**
- “Is the RISK^INDEX^ higher than, equal to, or lower than you expected?” - “Do you want to alter the medical treatment plan based on the RISK^INDEX^?” (yes/no) - “If yes, which part of the treatment plan?“ (reassessment during current ED visit; order additional investigations and consultations; admission or discharge; consultation with an ICU specialist and/or admission to ICU; removing or emplacing treatment restrictions) ^a^

ED, emergency department; ICU, intensive care unit

^a^ The physician will be asked to specify which part of the treatment plan was altered by choosing any of the given options

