### Statistical analysis

All analyses will be performed using the SPSS software (IBM Corp. Released 2021. IBM SPSS Statistics for Windows, version 28.0. Armonk, NY: IBM Corp).

The prognostic accuracy of the RISK^INDEX^ and the physician’s clinical intuition to predict adverse outcomes will be analyzed using an area under the receiver operating characteristics curve (AUC). To assess the clinical impact of the RISK^INDEX^, the number of changes in medical treatment based on the RISK^INDEX^ will be calculated. The prognostic accuracy of the RISK^INDEX^ will also be compared to that of the physician’s clinical intuition and to that of other clinical prediction models. Sub-analyses will be performed on the ED physicians’ characteristics, i.e. level of experience and function in relation to the accuracy of their clinical intuition. Summary estimates of effects will be presented along with their 95% confidence intervals (CI). Differences between the intervention and control groups will be presented in the form of an unadjusted mean difference for continuous outcomes, and an odds ratio for binary outcomes. Exploratory analysis using ANCOVA for continuous variables and logistic regression for binary outcomes will consider adjustment for the stratification variables in assessment of the treatment effects. Baseline characteristics will be summarized for all patients, and separately for the intervention group and control group. Feasibility and process evaluation data, such as practice recruitment rate, implementation and uptake of and adherence to the intervention, and follow-up rates will be summarized and presented as percentages.

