## Discussion

Rapid and accurate risk stratification at the ED is essential to optimize patient care and improving outcomes. Various prediction models, ranging from models based on a set of laboratory tests and vital signs (e.g. MEWS, SOFA, RISE UP) to emerging models based on ML have been proposed to aid in this stratification. Unfortunately, most of these models lack external validation, precision, or generalizability to the heterogeneous ED population [13]. In line with the emerging trend of ML technology based prediction models, we developed the RISK^INDEX^, a ML based prediction model that uses demographic characteristics (i.e. age and sex) and the results of laboratory tests available within the first two hours of ED presentation to create an individualized, precise and rapid risk estimation of 31-day mortality. The RISK^INDEX^ has externally been validated in three other hospitals, showing high prognostic accuracy (AUC ranging from 0.88 to 0.98) [16]. To the best of our knowledge, the MARS-ED study is the first prospective, randomized study to investigate the clinical impact of a ML based prediction model in the ED.

We aim to investigate the clinical impact of the RISK^INDEX^ by reviewing the number of changes in the medical treatment plan made as a result of presentation of the RISK^INDEX^ to the ED physician. In addition, we aim to prospectively investigate both the prognostic accuracy of the RISK^INDEX^ and the clinical impact of such a predictive model, and compare the RISK^INDEX^ to the physician’s clinical intuition. By randomizing the patients into an intervention group and a control group, we also aim to assess the clinical impact by comparing the treatment plan in both groups. The ultimate goal of this pilot study is to provide future studies with meaningful estimates of clinical impact of a ML based clinical prediction model.

While a limited number of retrospective studies have described attempts to use ML technology for risk stratification in the ED, none of these studies have been prospectively validated in a randomized setting [14, 15, 26, 27]. In other studies, ML based prediction models were developed with prognostic accuracies similar to our study (AUC of 0.96 and 0.93) [26, 27]. However, to our knowledge, no prospective, randomized trials validating these models have been conducted.

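### The 784-patient power statement compares treatment changes between the two groups, but that outcome is recorded in the intervention group only

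*Protocol article*

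**What the plan says.** The Sample size section of the protocol article states "a required sample size of 784 patients to detect a 2% difference in the number of changes in medical treatment" following presentation of the RISK INDEX, "between the control group and the intervention group with a power of 0.8". Patients are "randomized in a 1:1 ratio to the control group or the intervention group" (Trial design and setting).

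Under Study intervention and procedure, the index is shown to the physician in the intervention group only. Table 2 has two parts. The clinical-intuition questions go to both groups. The second part is headed "Questionnaire regarding medical treatment changes (intervention group only"; it asks whether the physician wants to alter the plan because of the index and, if so, which part of it.

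Study objectives and endpoints makes clinical impact part of the primary objective and lists "the number and type of changes in medical treatment after presentation of the RISK^INDEX^ to the ED physician" as a secondary objective. Statistical analysis measures clinical impact by counting treatment changes based on the index. Separately, it gives a general rule that group differences are reported as mean differences or as "an odds ratio for binary outcomes". The Discussion adds that "we also aim to assess the clinical impact by comparing the treatment plan in both groups". Data collection methods lists hospital admission, ICU admission, treatment restrictions and 31-day mortality for all patients.

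**The concern.** A power statement for a two-group difference needs the outcome to be observable in both groups. Here the outcome is defined by an event, presentation of the index, that does not happen in controls, and the only instrument that records it is not used in controls. The control value is either missing or set to zero by definition. In both cases it is not a measurement, and randomisation contributes nothing to the estimate.

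The article's only formal justification of size therefore describes a comparison that its own data collection cannot produce. The pilot is also meant to supply effect sizes for a later definitive trial. A between-group effect with no measured control rate would mislead that later calculation.

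**Working it through.** **Step 1. Is there a control value?**

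| Element | Intervention | Control |
|---|---|---|
| RISK INDEX shown to physician | yes | no |
| Clinical-intuition questions (Table 2, first part) | yes | yes |
| Treatment-change questions (Table 2, second part) | yes | no |
| Hospital admission, ICU admission, treatment restrictions (Data collection methods) | yes | yes |

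No intuition question asks about a plan or a change of plan. The last row is recorded in both groups, but it describes care delivered, not changes after presentation, and 784 is not stated for it. The powered outcome has no control observation.

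**Step 2. Can 784 be reproduced?**

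Inputs from the article: total 784, a difference of 2% (read here as 2 percentage points), power 0.8, 1:1 allocation. Not stated: alpha, control rate, method. I assume two-sided 5%; the article mentions only that "Summary estimates of effects will be presented along with their 95% confidence intervals (CI".

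Two proportions, pooled variance under the null:

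n per arm = [1.960·√(2p̄(1−p̄)) + 0.8416·√(p₀(1−p₀) + p₁(1−p₁))]² / (p₁−p₀)²

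For 0% versus 2%, p̄ = 0.01: [1.960·√0.0198 + 0.8416·√0.0196]² / 0.0004 = (0.2758 + 0.1178)² / 0.0004 = 387.3. This rounds up to 388 per arm, **776** in total.

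Other routes come as close or closer:
- Standardised difference of 0.2: 2·(1.96 + 0.84)² / 0.04 = 392 per arm, **784** in total (393 per arm, 786, with unrounded z values).
- 0% versus 2% with a Poisson-type variance: 784 to 786.
- Non-inferiority with a 2-point margin and 1% in both arms: 778.

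The article does not determine which of these was used.

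**Step 3. What would the power be if a control rate existed?**

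Power = Φ{[(p₁−p₀)·√n − 1.960·√(2p̄(1−p̄))] / √(p₀(1−p₀) + p₁(1−p₁))}

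The control rates are assumptions; the article gives none. The last column uses the expected enrolment of 1300.

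| Assumed control vs intervention | Total N for 80% power | Power, 392 per arm | Power, 650 per arm |
|---|---|---|---|
| 0% vs 2% | 776 | 0.805 | 0.953 |
| 0.5% vs 2.5% | 1158 | 0.635 | 0.844 |
| 1% vs 3% | 1538 | 0.516 | 0.731 |
| 2% vs 4% | 2282 | 0.375 | 0.561 |
| 5% vs 7% | 4426 | 0.217 | 0.329 |

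**Step 4. What can be estimated?**

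The proportion of intervention patients with at least one treatment change. Exact (Clopper–Pearson) 95% intervals at about 2%:
- 8/392 = 2.04%: 0.9% to 4.0%.
- 13/650 = 2.00%: 1.1% to 3.4%.

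**The case against.** The strongest defence is that this is an exploratory pilot. Its main purpose is to estimate recruitment, variability and effect sizes, and the planned numbers suit a one-arm estimate. That stands: no extra patients are needed, and the defect lies in the power sentence rather than in the number enrolled. But the article does make a formal between-group power claim, and the pilot label does not create a control observation.

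A second defence sets the control count to zero by definition, which is numerically compatible with 784. The control rate is then a constant, and what remains is a one-arm proportion.

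Four stronger readings are tempting but not supported:

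- *A reader might infer that 784 proves an assumed control rate of 0%.* That assumption gives 776 under the standard formula, and a standardised difference of 0.2 fits at least as well.
- *A reader might infer that the analysis will compute an undefined odds ratio, or test changes against an empty control cell.* The odds-ratio rule is general. The article says only that treatment changes will be counted, and assigns no test to them.
- *A reader might infer that no randomised comparison of treatment is possible.* Admission, ICU admission and treatment restrictions are collected in both groups and correspond to three of the five plan components in Table 2, so the comparison promised in the Discussion is partly feasible.
- *A reader might infer that the trial is sized on a merely secondary outcome.* Clinical impact is also a primary objective and is measured through these changes, so the outcome is listed at both levels.

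**Conclusion.** The power statement is wrong as written. The outcome it names is elicited in one group only, so a between-group power of 0.8 does not apply to it. This follows from setting Sample size against Table 2 and the study procedure, and does not depend on how 784 was obtained.

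The size of the problem can be shown only conditionally. Under assumed control rates of 0.5% to 5%, with two-sided 5% and a 2-point difference, power at 784 patients would fall from 64% to 22%. At 1300 it would run from 84% to 33%, so at the lowest of these rates the expected enrolment would still exceed 0.8. The conclusion is confined to the treatment-change outcome as defined and does not extend to every between-group comparison of care.

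**What to change.** 1. In Sample size, replace the two-group power statement with a precision statement for the proportion of intervention patients with at least one treatment change: exact 95% CI of about 0.9% to 4.0% for 8/392 and 1.1% to 3.4% for 13/650. Report it as a one-arm descriptive measure of clinical impact, and state that it will not be tested against the control group.
2. In Statistical analysis, base the randomised estimate of clinical impact on hospital admission, ICU admission and treatment restrictions, with 95% CIs. Do not attribute the 784-patient power to these outcomes.

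Both are changes of wording, with no extra patients and no new data. A question for control physicians is a separate option, not part of this low-cost fix. It could not repeat the Table 2 wording, which refers to the index. It might itself prompt a rethink and so affect usual care. It would also change the procedures of an ethics-approved trial, and power would have to be restated for a non-zero control rate.

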### Statistical analysis

All analyses will be performed using the SPSS software (IBM Corp. Released 2021. IBM SPSS Statistics for Windows, version 28.0. Armonk, NY: IBM Corp).

The prognostic accuracy of the RISK^INDEX^ and the physician’s clinical intuition to predict adverse outcomes will be analyzed using an area under the receiver operating characteristics curve (AUC). To assess the clinical impact of the RISK^INDEX^, the number of changes in medical treatment based on the RISK^INDEX^ will be calculated. The prognostic accuracy of the RISK^INDEX^ will also be compared to that of the physician’s clinical intuition and to that of other clinical prediction models. Sub-analyses will be performed on the ED physicians’ characteristics, i.e. level of experience and function in relation to the accuracy of their clinical intuition. Summary estimates of effects will be presented along with their 95% confidence intervals (CI). Differences between the intervention and control groups will be presented in the form of an unadjusted mean difference for continuous outcomes, and an odds ratio for binary outcomes. Exploratory analysis using ANCOVA for continuous variables and logistic regression for binary outcomes will consider adjustment for the stratification variables in assessment of the treatment effects. Baseline characteristics will be summarized for all patients, and separately for the intervention group and control group. Feasibility and process evaluation data, such as practice recruitment rate, implementation and uptake of and adherence to the intervention, and follow-up rates will be summarized and presented as percentages.

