## Introduction

The accurate assessment of the severity of the patient’s disease is an important challenge for physicians in the emergency department (ED). As the number of patients who visit the ED increases worldwide, crowding increases pressure on ED physicians, affecting not only patient satisfaction, but also placing the patient at risk of delayed treatment, increased in-hospital length of stay and increased mortality [1–5]. Fast and reliable discrimination between high and low risk patients may assist in proper allocation and management of resources, improving acute healthcare for patients in the ED.

Stratification of ED patients into low and high risk of poor outcome has traditionally relied on the clinical intuition of ED physicians and nurses [6]. However, previous studies have shown that ED physicians experience a high cognitive load, having to make important clinical decisions for their patients, often based on incomplete data, while being interrupted regularly and attending several patients at the same time [7–9]. Several clinical prediction models, e.g. modified early warning score (MEWS), sepsis-related organ failure (SOFA) score, and risk stratification in the ED in acutely ill older patients (RISE UP), have been developed to aid clinical decision-making [10–12]. Since many models have not been externally validated, their discriminatory performance may be overestimated. Furthermore, implementation of these models may be difficult because some of them have been developed for a specific diagnosis, which may not yet have been established in the ED. Given the heterogeneity of ED patients, finding a single prediction model that covers the entire clinical spectrum remains difficult [13].

Recently, machine learning (ML) technology has emerged as a promising approach to develop new prediction models [14, 15]. One such new prediction model, the RISK^INDEX^, has been developed at the Maastricht University Medical Center (MUMC+) [16]. The RISK^INDEX^ utilizes sex, age and routine laboratory tests from the ED to predict 31-day mortality. The RISK^INDEX^ was externally validated in three other medical centers demonstrating an AUC of 0.88 to 0.98 ^16^. Although ML based prediction models show great potential, to our knowledge, randomized clinical trials to investigate their actual clinical impact have rarely been performed.

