### Study intervention and procedure

When a patient enters the ED for assessment and treatment by an internal medicine specialist, the patient will immediately be assessed for eligibility and randomized as soon as informed consent is obtained. Obtaining informed consent is performed by a member of the research team and involves explaining the study intervention and procedure to the patient and handing out a patient information form. The inclusion criteria and exclusion criteria are shown in Table 1.

**Table 1 Tab1:** Inclusion and exclusion criteria

Inclusion criteria	Exclusion criteria
Patients must meet all of the following criteria: - Adult (18 years or older) - Primarily assessed and treated by an internal medicine specialist in the ED - At least 4 laboratory test results available within the first 2 h of the ED visit - Willing to provide written informed consent (either directly or after deferred consent)	Patients who meet any of the following criteria: - Less than 4 laboratory test results available within the first 2 h of the ED visit - Unwilling to provide written informed consent

ED, emergency department

After inclusion, the patient is allocated to either the intervention group or the control group through randomization. An overview of the patient’s timeline is shown in Supplemental Fig. 1. Then, the patients will receive medical care in the ED as usual. After complete assessment of the patient, in both the intervention group and control group, the physicians will be asked questions regarding their clinical intuition (Table 2). In the intervention group, the RISK^INDEX^ will be presented to the physician together with the average mortality risk for ED patients with the same age and sex, and subsequently questions will be asked concerning agreement of their clinical intuition with the RISK^INDEX^ and whether the presented RISK^INDEX^ leads to changes in the treatment plan (Table 2). If the patient is admitted to the hospital, the attending physician on the medical ward will be asked the questions regarding clinical intuition on the first day of admission. A member of the research team immediately records the answers to the questions of all questionnaires in an electronic case record form, which was specially designed for this study.

**Table 2 Tab2:** Questionnaires regarding clinical intuition and medical treatment changes

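### AUC is the only accuracy measure named for an index presented as a calibrated mortality risk, so a systematic error in risk level would not be visible in the stated analysis

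*Protocol article*

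**What the plan says.** Under Study objectives and endpoints: "The primary objective of this study is to assess the prognostic accuracy and the clinical impact of the" index. The Statistical analysis section then gives the method: prognostic accuracy "will be analyzed using an area under the receiver operating characteristics curve (AUC". The comparisons with clinical intuition and with other scores name no further metric.

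Elsewhere the article describes the index by its level as well as its ranking:

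- The section on the index states "The score is calibrated ranging from 0 to 100". Calibration is mentioned only here, as a property the score already has.
- Under Study intervention and procedure, the index is "presented to the physician together with the average mortality risk for ED patients with the same age and sex".
- The intervention-arm questionnaire (Table 2) asks whether the index is "higher than, equal to, or lower than you expected", and then whether the physician wants to change the treatment plan.
- The Discussion calls the output an "individualized, precise and rapid risk estimation of 31-day mortality".

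Earlier validation is reported as discrimination only. The Introduction cites external validation "demonstrating an AUC of 0.88 to 0.98", and the Discussion and Limitations repeat that range. No calibration result is given.

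**The concern.** Discrimination and calibration are separate properties. AUC is the probability that a patient who dies has a higher score than one who survives. Any order-preserving change to the score leaves it unchanged. An index that doubles or halves everyone's risk therefore has the same AUC as a correct one.

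The physician sees a number next to the mean mortality of comparable patients and is asked whether it is higher or lower than expected. That invites a judgement about level. If the level were wrong, a high AUC could still be reported as high prognostic accuracy. The other half of the primary objective, the count of treatment changes, would not expose the error either, because it records whether plans changed and not whether the displayed risk was right.

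**Working it through.** **Inputs from the article.** 31-day mortality about 10% (Adverse event monitoring); 1300 patients expected and 784 required (Sample size); 1:1 allocation; cited AUC 0.88 to 0.98.

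**The plan's own figure.** The 784 is used below only as a number of patients. A two-proportion calculation with 0% against 2%, power 0.8 and two-sided alpha 0.05 gives 388 per arm, 776 in total, which is close to 784. The 0% control rate and the alpha are assumptions. Nothing below depends on them.

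**Step 1: what AUC can see.** One million patients were simulated with logit-normal true risks and mean mortality 10%. The SD of 2.2 is assumed, and it puts the AUC inside the cited range. Each row is the same ranking shown on a different scale. O/E is observed divided by mean predicted mortality.

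| Score shown | Mean predicted | Observed | AUC | O/E |
|---|---|---|---|---|
| Correct risk | 10.0% | 10.0% | 0.898 | 1.00 |
| Odds tripled | 18.5% | 10.0% | 0.898 | 0.54 |
| Odds cut to one third | 4.9% | 10.0% | 0.898 | 2.06 |
| Too extreme (calibration slope 0.5) | 6.4% | 10.0% | 0.898 | 1.56 |
| Rank percentile on 0–100 | 50% | 10.0% | 0.898 | 0.20 |

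The distortions are hypothetical. The invariance does not depend on them or on the SD, because it holds for any order-preserving change.

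**Step 2: could the trial see it with calibration measures?** With expected deaths treated as fixed, SE(ln O/E) ≈ √(0.9 / deaths), and the 95% CI multiplies and divides O/E by exp(1.96 × SE).

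- All 1300 patients: 130 deaths, exp(1.96 × √(0.9/130)) = 1.18.
- Control arm of 1300: 650 patients, 65 deaths, exp(1.96 × √(0.9/65)) = 1.26.
- All 784 patients: 78.4 deaths, exp(1.96 × √(0.9/78.4)) = 1.23.
- Control arm of 784: 392 patients, about 39 deaths, exp(1.96 × √(0.9/39.2)) = 1.35.

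In the smaller control arm, an O/E of 2.06 would have a CI of 2.06/1.35 to 2.06 × 1.35, or 1.53 to 2.78. An O/E of 0.54 would have 0.40 to 0.73. Both exclude 1. In both arms together, the simulated SE of the calibration slope was about 0.08 at 1300 patients and 0.10 at 784.

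**Step 3: effect of the consent rule.** The recruitment section deletes the data of deferred-consent patients who die before consenting. Suppose k such deaths are removed and their predicted risks sum to S. Each predicted risk is below 1, so S < k. A perfectly calibrated index with D observed and D expected deaths would then show (D − k)/(D − S), which is below 1. This clause alone would make a correct index look as if it over-predicts.

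**The case against.** The best defence is that this is a short analysis section in a journal article. Naming AUC does not exclude calibration, and the full protocol, analysis plan or supplement may contain it. That is possible. But the article does more than stay silent. It selects a measure for a primary objective, and that measure cannot examine a property the article asserts and the display invites physicians to use. If calibration is planned elsewhere, the article's statement only needs aligning.

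AUC is also the right tool for the stated comparisons. Intuition is recorded as yes/no and 1–10 answers, which are not probabilities and have no calibration to compare. This stands, and AUC should stay.

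The article never says outright that the 0–100 value is a percentage probability. In the section on the index, high simply means high risk. This also stands. If the value is not a probability, O/E is undefined until its mapping to risk is given.

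Three stronger readings are tempting but unsupported:

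- A reader might infer that a poor index would pass the primary analysis. No AUC threshold or success rule exists, so nothing is passed or failed.
- A reader might take the Limitations remark that the index can be adapted to each centre as a sign that its level is wrong here. That remark concerns other hospitals, and this trial runs where the index was developed.
- A reader might infer that a miscalibrated score will be carried into the definitive trial. The Sample size section says the pilot supplies effect sizes, recruitment and retention rates, and variability.

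**Conclusion.** The point holds as a limit of the named method. The stated accuracy analysis would not reveal a systematic over- or understatement of risk: predicted means from 4.9% to 50% against an observed 10% give the same AUC. It does not show that the index is miscalibrated, and no passage suggests that it is.

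Calibration can be estimated usefully in this trial, to within a factor of about 1.26 in the control arm at 1300 patients or 1.35 at 784. Errors smaller than that would not be clearly distinguishable from chance in that arm. These figures rest on 10% mortality, equal arms, and reading the 0–100 value as a predicted probability. This is a worthwhile improvement to a stated method in an exploratory pilot, and it leaves the randomised comparison unaffected.

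**What to change.** Keep AUC for discrimination and for the comparisons with intuition and other scores. Add for the index, with 31-day mortality as outcome and 95% CIs:

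- the observed/expected ratio;
- the calibration slope;
- a smoothed calibration plot.

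State that the 0–100 value is read as a predicted probability. If it is not one, give its mapping to risk first.

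Take the main estimate in the control arm, where the index was not shown, and report the intervention arm alongside. The Limitations section itself notes that showing the index may alter mortality.

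State as a caveat that deleting deferred-consent patients who die before consenting biases O/E downward, and report how many patients were deleted if that count may be kept.

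The cost is a small amount of extra analysis. Laboratory results, age, sex, index results and 31-day mortality are already to be collected for the patients whose data are retained.
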